## Abstract

**Background:**

In adults, treatment of GHD with daily GH injection has been shown to improve many clinical features associated with GHD. Currently, many adults with GHD receive GH treatment indefinitely. Short and medium-term studies have demonstrated beneficial effects of GH replacement therapy, including improvements in body composition, metabolic parameters and quality of life. However, uncertainty remains regarding the long-term sustainability of these benefits and the consequences of treatment discontinuation. A randomised controlled trial is needed to understand the impacts of discontinuing long-term GH therapy in adults. Prior to embarking on an RCT, the feasibility of a discontinuation study and the acceptability of randomisation to patients and clinicians need to be assessed. Research aims (a) to explore the current practice of offering discontinuation of long-term GH treatment in adults in the UK and (b) to assess the feasibility of conducting an RCT evaluating GH treatment discontinuation in adults with GHD.

**Methods:**

This multi-method study comprises of three phases.
•Phase 1: An online survey of endocrine clinicians’ practice of offering discontinuation of long-term GH therapy in adult patients with GHD.•Phase 2: Feasibility cohort study involving two groups of adult patients with GHD (aged more than 25 years), who have been on GH treatment for at least 5 years.: (a) an intervention group consisting of 20–25 patients who will be discontinuing their long-term GH treatment for two years and (b) a control group consisting of 20–25 patients who will continue with their GH treatment.•Phase 3: Qualitative study. 10–16 participants will be recruited to explore their experiences of participation in the feasibility study using semi-structured interviews.

Potential benefits This study will provide evidence of current GH treatment discontinuation practice in the UK and determine the feasibility of any future RCT. Long-term, this could promote and underpin the development of the much-needed relevant clinical guidance.

## Introduction

Growth hormone deficiency (GHD) in adults is caused by decreased secretion of growth hormone (GH) from the pituitary gland.
^1^
^,^
^2^ This condition is usually caused by a tumour, surgery and/or radiotherapy involving the pituitary gland.
^3^ Adults with GHD present with a constellation of several non-specific features including low mood, poor general well-being, reduced bone mineral density (BMD), increased body fat, increased cholesterol level and reduced exercise capacity.
^3^
^–^
^5^ Treatment with recombinant human growth hormone (GH) injection has been shown, in short-term studies, to improve the wide spectrum of health issues associated with GHD.
^6^

In the UK, the National Institute for Health and Care Excellence (NICE) recommends treating adult patients with GHD with GH until peak bone and muscle mass have been achieved (estimated to be at around the age of 25 years).
^7^ For adults over 25 years old, the prescribing of GH treatment is based on NICE criteria that requires patients to: a) have severe GHD, defined in the UK according to NICE guidance, as a peak GH response of less than 9 mU/litre during a GH stimulation test; b) have a perceived impairment of quality of life (QoL), as demonstrated by a score of at least 11 in the ‘Quality of Life - Adult Growth Hormone Deficiency Assessment’ (QoL-AGHDA) questionnaire; c) be receiving appropriate treatment for any other pituitary hormone deficiencies. The UK population of adult patients with GHD receiving GH is quite unique and homogenous as they all have severe GHD and poor quality of life (QoL) prior to commencing the treatment.
^4^ The UK is the only country in the world that offers GH to adult patients with GHD only after poor QoL scores have been confirmed by using the QoL-AGHDA questionnaire.
^1^
^,^
^4^
^,^
^6^

To date, the optimal duration of GH replacement therapy in adults and the consequences of treatment withdrawal have not been established. There are only a few, mainly short-term, follow-up studies that provide conflicting results. Overall, the beneficial effects of GH treatment appear to occur during the first year of therapy with only a few studies reporting sustained benefits up to 5 years.
^5^
^,^
^8^
^–^
^10^ It is well established that GH secretion decreases in a normal population with advancing age and that low GH levels are even associated with increased longevity and decreased morbidity.
^11^
^,^
^12^ Currently, many adults with GHD are receiving GH indefinitely without knowing if continuing or discontinuing long-term treatment has sustained beneficial or even adverse effects.
^13^
^,^
^14^ Similarly, reliable data on the impact of discontinuing long-term GH therapy in adults is not available.

In the UK, provided that a 7-point improvement (or higher) on the 25-point QoL-AGHDA scale is demonstrated during the first 9 months of GH therapy, adult patients with GHD can continue with their GH treatment long-term.
^7^ However, it remains uncertain if the beneficial effects of GH therapy are sustained throughout adult life, as robust evidence on the risks and benefits of long-term GH treatment is limited. Furthermore, the evidence of improved QoL in adult patients with GHD having GH treatment over placebo has not been established.
^6^ Anecdotally, clinicians report encountering patients who question the merit of continuing with long-term GH treatment. Paradoxically, the same patients are apparently reluctant to stop GH therapy due to fears of return of symptoms and uncertainty about the short-term and long-term effects of treatment discontinuation. Consequently, and in the absence of clear evidence and definitive guidance, replacement therapy with GH continues indefinitely in many adults.

## Rationale

Many questions on the effectiveness of long-term treatment with GH in adults remain unanswered including its optimal duration and the consequences of treatment discontinuation. The primary aim of this study is to assess the feasibility of conducting a large-scale multi-centre study to evaluate the effects of discontinuation of long-term GH therapy on the metabolic profile, body composition and QoL in a cohort of adult patients with GHD (aged 25 years and over) over a period of 24 months.

Currently, much of the evidence on safety-related issues associated with long-term GH therapy comes from uncontrolled retrospective, and observational studies, which are methodologically inferior compared with randomised control trial (RCT).
^1^
^,^
^6^ A critical assessment of data from limited RCTs did not show consistent beneficial effects of GH therapy in adult patients with GHD compared with placebo.
^6^ In 2016, several international endocrine societies collectively highlighted the need for carefully designed and rigorously conducted cohort studies to monitor the safety of long-term GH therapy.
^15^ Furthermore, treatment of adults with GHD is also associated with significant health care costs. In the UK, the average annual cost of GH treatment in adults is estimated to be around £3,350 per patient, with a life-long therapy cost of between £42,000 and £45,400.
^7^ Furthermore, the treatment regimen of daily self-injections can be inconvenient and burdensome for many patients.
^14^
^,^
^16^

Despite ongoing uncertainty regarding the optimal duration of treatment and the long-term consequences of treatment withdrawal, the efficacy and safety of GH replacement therapy in appropriately selected patients with GHD are well established. Previous studies have demonstrated favourable effects on body composition, metabolic health, bone health and quality of life in adults with GHD, while extensive post-marketing surveillance and longitudinal follow-up studies have generally supported an acceptable safety profile.
^1^ The present study does not seek to challenge the established role of GH replacement therapy, but rather to address persistent uncertainties regarding its optimal duration and the effects of treatment discontinuation.

The current NICE guidance provides clear criteria for commencing GH treatment for adults with GHD. However, it does not offer any recommendations on the optimal duration of GH treatment in adults or if and when discontinuation should be considered. Consequently, GH replacement therapy tends to be offered indefinitely even when patients fail to report any sustained benefits from this treatment. Given that GH treatment is associated with significant health care costs, it is imperative to clearly establish the clinical and cost-effectiveness of the therapy. A methodologically robust and well-designed large-scale multi-centre study will contribute this evidence. However, Medical Research Council guidelines suggest that feasibility studies are required to test the methodology and establish the specific parameters prior to any full large-scale multi-centre study.
^17^ The strict criteria for prescribing GH to adults and the homogeneity of the UK population of adults with GHD, offers an ideal setting to undertake a robust study.

## Protocol

This is a sequential multi-methods study which will be conducted in three phases:
•Phase 1: Survey of endocrine clinicians•Phase 2: Observational feasibility cohort study•Phase 3: Qualitative study

### Phase 1: Survey of endocrine clinicians

The aim of this phase is to understand the current practice of endocrine clinicians in the UK of offering GH treatment discontinuation in adults with GHD who have been prescribed long-term replacement therapy. It will also determine the willingness of endocrine clinicians in the UK to take part in future large-scale multi-centre study.

## Methods

A multiple-choice questionnaire has been developed drawing on current guidance, gaps in the evidence, as well as expert clinicians’ opinion. The survey questions have been reviewed for content validity by expert clinicians who are involved in the study centre’s Growth Hormone Clinic and by members of the GAMBOL Patient and Public Advisory Group (PPAG). Formal endorsement will be sought from the Society for Endocrinology (SfE) to allow the survey to be sent to all endocrine clinicians (doctors and nurses) on the Society’s contact list using Survey Monkey
^®^. The questionnaire has been designed to ascertain the following:
•the number of adult patients treated with GH in different endocrine centres in the UK who have been on replacement therapy for more than 5 years;•the current practice and criteria used by endocrine clinicians in offering a period of GH treatment discontinuation in adults;•the interest of endocrine clinicians in taking part in future a large-scale multi-centre study on GH treatment discontinuation in adults.

**
*Survey administration*
**

Following approval by the SfE, the link to the Survey Monkey
^®^ online survey will be sent to all endocrine clinicians in the UK registered on the SfE membership database. Information will also be posted on the SfE website and on the endocrine nurses’ closed Facebook
^®^ forum. The survey is planned to be available for 8 weeks.

**
*Data collection and analysis*
**

Data will be collated from the survey and presented as frequencies and percentages. Descriptive data will be presented in themes when applicable. Respondents will also be asked to indicate the approximate number of adults with GHD managed within their service. Survey responses may be explored descriptively according to centre size and clinical experience to identify potential variations in practice.

**
*Presentation and dissemination*
**

Survey results will be presented initially at the study centre’s endocrine department’s monthly meeting. The results will also be presented at the Pituitary Foundation patient group meeting that takes place quarterly in Birmingham. An abstract will be submitted at the SfE congress highlighting the key findings from the survey.

### Phase 2: Observational feasibility cohort study

This phase will be conducted over 32 months to allow steady recruitment of adequate number of study participants, completion of outcome measures and evaluation and assessment of patients’ body composition (BMD [lumbar spine and both hips], muscle mass and fat mass [whole body] using DXA scan), at baseline and at two years. The 2-year interval for DXA scanning is necessary as reassessing patients’ BMD earlier would likely fail to capture any measurable significant changes.
^15^

**
*Primary aim*
**

To assess the feasibility of conducting a large-scale multi-centre study on discontinuation of long-term GH treatment in adult patients with GHD.

**
*Secondary aim*
**

To assess the impact of discontinuing long-term GH treatment on the metabolic profile, body composition and QoL in adult patients with GHD.

#### Objectives

•To assess the rate of patient recruitment, retention and withdrawal.•To identify barriers for recruiting and retaining participants into the study.•To assess the suitability and acceptability for patients of the frequency of follow-up and assessment.•To assess the suitability and acceptability for patients of the QoL questionnaires.•To assess the study protocol including recruitment, biochemical monitoring, body composition monitoring, and QoL assessment.•To assess the safety of GH treatment discontinuation in adult patients with GHD.

**
*Study participants*
**

The study will recruit a total of three groups of adult patients with GHD (aged 25 years and over).
I.
**
*Group 1-
Discontinuation group*
**: 20–25 patients who have been on GH therapy for 5 years or longer and voluntarily agree to discontinue their GH treatment and be monitored for two years.II.
**
*Group 2-
Continuation group*
**: 20–25 patients who have been on GH therapy for 5 years or longer and voluntarily agree to take part in the study, where their GH treatment is continued and are monitored in the same way as the discontinuation group.III.
**
*Group 3-
Continuation group following initial discontinuation*
**: patients who were initially part of the discontinuation group (Group 1) and decided to withdraw from the study, due to adverse effects of GH discontinuation, and restart their treatment. Patients monitoring will continue in the same way as the continuation group for a total of two years from the time they initially enrolled in the study.

**
*Study Visits*
**

Visit 1
•Patients attend endocrine outpatient clinic on the morning of the study visit after an overnight fast (fasted for at least 8 hours prior to study visit).•Informed consent will be re-confirmed.•Patients who do not consent to take part in the study will be referred back to the endocrine clinic to continue standard care monitoring.•Following confirmation of consent, a standardised physical assessment, medical and medication histories will be completed to re-confirm inclusion/exclusion criteria.•Study participants will undergo the following anthropometric assessments and all results will be recorded on the patient’s electronic health records: height; weight; BMI; blood pressure and, waist and hip circumferences. Height will be measured to the nearest centimetre (cm) using a wall-mounted meter. Weight will be measured in kilograms (kg) (to one decimal place) using an electronic scale. Waist circumference will be measured midway between the lower margin of the last palpable rib and the top of the iliac crest, and hip circumference at the level of the greater trochanters to the nearest cm. Blood pressure will be measured using an automated blood pressure monitor (Omron 705IT sphygmomanometer or equivalent). Blood pressure measurements will be performed at sitting position after a few minutes rest.•Blood samples for research will be taken which include: insulin growth factor-1 (GF-1); high density lipoprotein (HDL); low density lipoprotein (LDL); total cholesterol; triglyceride; glycated haemoglobin A1c (HbA1c), and fasting glucose. For these purposes, blood samples will be drawn using one purple top EDTA tube (4 mL × 1 = 4 mL), one fluoride oxalate grey top tube (4 mL × 1 = 4 mL), one yellow top tube (6 ml × 1 = 6 mL) and 1 red top tube (6 mL × 1 = 6 mL). A total of 4 blood tubes will be drawn with a total volume of 20 mL.•LDL cholesterol will be calculated using the laboratory’s standard validated method from the fasting lipid profile.•Study participants will complete three QoL assessment questionnaires which include: QoL-AGHDA (5 minutes); Treatment-Related Impact Measure Adult Growth Hormone Deficiency (TRIM-AGHD) (5 minutes) and, SF-36 (10 minutes).•Study participants will undergo body composition assessment using DXA scan to measure BMD at the lumbar spine and both hips, as well as fat mass and muscle mass of the whole body. BMD and fat and muscle mass measurements will be completed in one DXA appointment.•Appointment for study visit 2 (at 6 months [+/− 2 weeks]) will be arranged and confirmed.

Visits 2–4 (6-monthly visit) (between 08.00 AM – 12.00 Noon)
•Visits 2–4 will take place at month 6, 12 and 18 respectively (+/− 2 weeks).•To allow some flexibility and to accommodate the study participant’s availability, each follow-up study visit can take place up to two weeks earlier or two weeks later than the planned scheduled visit.•Study participants attend endocrine outpatient clinic on the morning of the study visit after an overnight fast (fasted for at least 8 hours prior to study visit).•Re-confirm consent and eligibility criteria.•A standardised physical assessment, medical and medication histories will be completed to assess for adverse events and to confirm each study participant’s suitability and willingness to continue with the study.•Study participants will undergo the following anthropometric assessments and all results will be recorded on the patient’s electronic health records: height; weight; BMI; blood pressure and, waist and hip circumferences. Height will be measured to the nearest centimetre (cm) using a wall-mounted meter. Weight will be measured in kilograms (kg) (to one decimal place) using an electronic scale. Waist circumference will be measured midway between the lower margin of the last palpable rib and the top of the iliac crest, and hip circumference at the level of the greater trochanters to the nearest cm. Blood pressure will be measured using an automated blood pressure monitor (Omron 705IT sphygmomanometer or equivalent). Blood pressure measurements will be performed at sitting position after a few minutes rest.•Blood samples for research will be taken which include: IGF-1; HDL; LDL; total cholesterol; triglyceride; HbA1c, and fasting glucose. For these purposes, blood samples will be drawn using one purple top EDTA tube (4 mL × 1 = 4 mL), one fluoride oxalate grey top tube (4 mL × 1 = 4 mL), one yellow top tube (6 ml × 1 = 6 mL) and 1 red top tube (6 mL × 1 = 6 mL). A total of 4 blood tubes will be drawn with a total volume of 20 mL.•Study participants will complete three QoL assessment questionnaires which include: QoL-AGHDA (5 minutes); TRIM-AGHD (5 minutes) and, SF-36 (10 minutes).•Appointment for study visit 5 will be arranged and confirmed.

Visit 5 (month 24 [+/− 2 weeks]) (between 08.00 AM – 12.00 Noon)
•To allow some flexibility and to accommodate the study participant’s availability, as well the availability of slots for DXA scan appointment, this final study visit can take place up to two weeks earlier or two weeks later than the planned scheduled visit.•Study participants attend endocrine outpatient clinic on the morning of the study visit after an overnight fast (fasted for at least 8 hours prior to study visit).•Re-confirm consent and eligibility criteria.•A standardised physical assessment, medical and medication histories will be completed to assess for adverse events.•Study participant will undergo the following anthropometric assessments and all results will be recorded on the patient’s electronic health records: height; weight; BMI; blood pressure and, waist and hip circumferences. Height will be measured to the nearest centimetre (cm) using a wall-mounted meter. Weight will be measured in kilograms (kg) (to one decimal place) using an electronic scale. Waist circumference will be measured midway between the lower margin of the last palpable rib and the top of the iliac crest, and hip circumference at the level of the greater trochanters to the nearest cm. Blood pressure will be measured using an automated blood pressure monitor (Omron 705IT sphygmomanometer or equivalent). Blood pressure measurements will be performed at sitting position after a few minutes rest.•Blood samples for research will be taken which include: IGF-1; HDL; LDL; total cholesterol; triglyceride; HbA1c, and fasting glucose. For these purposes, blood samples will be drawn using one purple top EDTA tube (4 mL × 1 = 4 mL), one fluoride oxalate grey top tube (4 mL × 1 = 4 mL), one yellow top tube (6 ml × 1 = 6 mL) and 1 red top tube (6 mL × 1 = 6 mL). A total of 4 blood tubes will be drawn with a total volume of 20 mL.•Study participants will complete three QoL assessment questionnaires which include: QoL-AGHDA (5 minutes); TRIM-AGHD (5 minutes) and, SF-36 (10 minutes).•Study participants will undergo body composition assessment using DXA scan to measure BMD at the lumbar spine and both hips, as well as fat mass and muscle mass of the whole body. BMD and fat and muscle mass measurements will be completed in one DXA appointment.•This will be the end of phase two study visits.•Participants who are eligible to take part in the phase 3 of the study will be approached. Interested participants will be provided with patient information sheet and will have a minimum of 72 hours to decide if they wish to participate. Potential participants will be contacted by phone after 72 hours to confirm their willingness to take part in the phase 3 of the study and patients who confirmed their willingness for this will be booked an appointment for either a face-to-face, a telephone or a virtual (via Microsoft Teams) interview (according to participant’s preference). Any patient who wishes to have more time to consider the study will be given a further 72 hours.

**
*Data collection and analysis*
**

Data will be collected and stored in the study centre’s secured and password protected server. A GAMBOL study data sheet will be generated using REDCap® which is password protected. All data will be pseudo-anonymised. Data analysis will involve descriptive statistics and presented as means ± standard deviation (SD) for continuous variables that are normally distributed, and as medians with interquartile (25th and 75th percentile) range for continuous variables that are skewed. Between-group differences will be analysed using independent samples t test and analysis of covariance (ANCOVA) test. Categorical variables will be presented as frequencies and percentages. A statistician from UHB has agreed to provide support for this study.

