### Sampling

**
*Size of sample*
**

As this is a feasibility study, a formal power calculation is not required.
^20^ A maximum of 25 patients in each group (50 in total) will be recruited in the phase 2 which is at the upper end of the numbers recommended for pilot/feasibility studies.
^21^ 5–8 participants who completed the phase 2, and similar number of participants who withdrew from phase 2, will be invited to participate in the phase 3 of the study.

**
*Sampling technique and recruitment*
**

Phase 2 (Observational Feasibility Cohort Study): purposive case sampling will be used to recruit study participants. Eligible patients will be identified from endocrine outpatient clinic lists and from the endocrine database of patients on growth hormone treatment. Patients who are willing to take part in the study will be given the choice of taking part in either the discontinuation group or the continuation group. Patients withdrawing from the discontinuation group will be invited to continue on the study for on-going monitoring.

Phase 3 (Qualitative Study: Interview): purposive sampling will be used to recruit study participant. Participants will be recruited from those taking part in the phase 2 of the GAMBOL study. Participants will be approached at the point of completing the phase 2 (study visit 5), whereas those who are withdrawing from phase 2 of the study will be approached at the point of withdrawal.

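### An unadjusted t test is given equal standing with ANCOVA for comparing groups that patients chose themselves, under an aim worded as the impact of stopping GH

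*Protocol article*

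**What the plan says.** The Phase 2 paragraph on data collection and analysis (Protocol article) sets the method for comparing the groups: "Between-group differences will be analysed using independent samples t test and analysis of covariance (ANCOVA) test". It does not restrict the t test to particular variables or to a descriptive role, and it does not say which of the two methods leads.

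The section on sampling technique and recruitment says how the groups arise: willing patients "will be given the choice of taking part in either the discontinuation group or the continuation group". The design is labelled "Observational feasibility cohort study".

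Two aims are given for Phase 2. The primary aim is "To assess the feasibility of conducting a large-scale multi-centre study on discontinuation of long-term GH treatment in adult patients with GHD". The between-group comparison serves the secondary aim: "To assess the impact of discontinuing long-term GH treatment on the metabolic profile, body composition and QoL in adult patients with GHD". On size, the article says "A maximum of 25 patients in each group (50 in total) will be recruited in the phase 2".

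**The concern.** Allocation by preference is unlikely to be neutral. The Introduction describes patients who doubt the value of continuing GH and who nevertheless hesitate to stop because they fear that symptoms will return. Phase 3 makes the reasons for choosing a group an object of study. Perceived benefit and quality of life may therefore influence the choice, and quality of life is also an outcome.

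A t test between such groups estimates the effect of stopping plus whatever separated the choosers at the start. The second part does not shrink as the sample grows, and no covariate list in a document not shown can repair it, because the t test takes no covariates. With two methods on the same footing, the results can disagree most when the groups are imbalanced at baseline, which is when the choice between them matters most. At stake is what the next trial's designers take from Phase 2 about the consequences of stopping.

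**Working it through.** **Figure in the article.** The only relevant number is the maximum sample: 2 × 25 = 50, which agrees with the text. No error rate is stated, so there is none to reproduce. What follows is an illustration on stated assumptions.

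**Inputs from the article.** Unadjusted t test; self-chosen groups; 20 to 25 per group; outcomes measured at baseline and at month 24. The article does not say whether month-24 values or changes from baseline are compared, so both are shown.

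**Assumptions (not in the article).** Two-sided 5% test; no true effect of stopping; baseline and month-24 values each with SD 1 within groups; standardised baseline difference b = 0.3, 0.5 or 0.8 between choosers; baseline to month-24 correlation r = 0.5 or 0.7.

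**Formulas.**
- Month-24 values: spurious difference d = b × r.
- Change scores: the spurious difference is (r − 1) × b, and the SD of the change is √(2(1 − r)), so d = (r − 1)b / √(2(1 − r)).
- The rejection rate comes from the non-central t distribution with 2n − 2 degrees of freedom and non-centrality d × √(n/2).

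**One case in full** (n = 25, b = 0.5, r = 0.7), with √(25/2) = 3.536:
- Month-24 values: d = 0.5 × 0.7 = 0.35; non-centrality 0.35 × 3.536 = 1.24 on 48 degrees of freedom; rejection rate 22.8%.
- Change scores: d = −0.3 × 0.5 / √0.6 = −0.15 / 0.775 = −0.194; non-centrality −0.68; rejection rate 10.3%.

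**Grid at 25 per group.**

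| b | r | d, month-24 | rejects | d, change | rejects |
|---|---|---|---|---|---|
| 0.3 | 0.5 | 0.15 | 8.1% | −0.15 | 8.1% |
| 0.3 | 0.7 | 0.21 | 11.3% | −0.12 | 6.9% |
| 0.5 | 0.5 | 0.25 | 13.9% | −0.25 | 13.9% |
| 0.5 | 0.7 | 0.35 | 22.8% | −0.19 | 10.3% |
| 0.8 | 0.5 | 0.40 | 28.3% | −0.40 | 28.3% |
| 0.8 | 0.7 | 0.56 | 49.2% | −0.31 | 18.9% |

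At 20 per group the month-24 range is 7.5% to 40.8%, and the change-score range is 6.5% to 23.4%. The two versions of the t test err in opposite directions: month-24 values carry the imbalance forward, while change scores over-correct for it.

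**ANCOVA on the baseline value** (simulation, 20,000 runs, n = 25, r = 0.7, no true effect). With b = 0.5 it rejects 5.2% of the time, against 22.9% for the t test on month-24 values. With b = 0.8 the figures are 5.0% and 49.1%.

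**Limit of the remedy.** Add a 0.3 SD difference at month 24 from a factor outside the model (b = 0.5, r = 0.7). ANCOVA then rejects 29.0% of the time and the t test 61.1%.

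**The case against.** The strongest reply is that the same sentence names ANCOVA, which is the adjusted method a reviewer would ask for. That stands. It would be wrong to say that the plan relies on an unadjusted t test alone.

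A reader might also infer that group differences will be reported as treatment effects. The article does not say so. It speaks of between-group differences in a study labelled observational, with feasibility as its primary aim. Only the word impact in the secondary aim points towards the causal reading.

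The covariates, the outcome form and the order of the analyses may sit in a full protocol or analysis plan that is not shown, so their absence is not held against the article. Such a document could demote the t test, but it could not adjust it.

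Three further inferences fail. The article plans medians and quartiles for skewed variables, but does not say that these enter the tests untransformed. It gives no significance level or schedule of tests, so a count of expected false positives would be the reader's own construction. And low power is no defect in a study that states "As this is a feasibility study, a formal power calculation is not required".

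Finally, baseline adjustment cannot remove unmeasured reasons for choosing a group, as the last simulation shows. That limits what the fix achieves, but it does not favour the t test, which did worse in the same setting.

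**Conclusion.** The point holds in this form: for self-selected groups, and under an aim worded as impact, the article commits to an unadjusted t test on an equal footing with ANCOVA. The t test cannot separate selection from the effect of stopping.

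On the stated assumptions, the false-positive rate at 25 per group is about 8% to 49% on month-24 values and about 7% to 28% on change scores, against about 5% for baseline-adjusted ANCOVA. The 5% holds only if the baseline value is the sole confounder. The imbalance, correlation and significance level are illustrative. If the choosers turn out alike at baseline, the inflation that arises from the baseline value disappears.

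The importance is moderate, because the comparison serves a secondary aim of a feasibility study. Multiplicity, skewness and power are not part of this finding.

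**What to change.** Reword the Phase 2 analysis paragraph as follows:
- Make one ANCOVA per outcome the lead analysis, adjusted for the baseline value of that outcome and a few prespecified covariates such as age, sex and years on GH. With at most 50 patients the list should be short.
- Remove the t test as an inferential analysis; keep the unadjusted comparison as description at most.
- Report adjusted differences with 95% confidence intervals as exploratory associations, and word the secondary aim to match.
- State that patients chose their group and that confounding by unmeasured reasons for that choice remains.

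The cost is a change of wording and a few degrees of freedom. Baseline outcome values are collected at Visit 1, date of birth and sex are already recorded, and treatment length has to be established for eligibility. The change should be made before the Phase 2 data are analysed. According to the trial status section, that analysis begins four weeks after the last participant's final visit.
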